#### Data analysis

In line with Braun and Clarke’s method for thematic analysis [69], qualitative data collected from semi-structured interviews and exit questionnaires will be coded and analysed. Themes and sub-themes will be identified by two members of the research team. To ensure reliability of themes, an independent investigator not otherwise involved in the study will review a sub-set of the transcripts (10%) and consensus reached. Questions included in the exit questionnaire which utilises a Likert scale will be scored and the overall percentage of participants who selected specific statements will be reported.

## Results

Participant flow through the study is detailed in Fig. 1. Recruitment of participants will begin in August 2021 and is expected to last until December 2022. Data analyses are expected to begin in early 2023.

## Discussion

We have presented the rationale and design of a pilot randomised controlled trial which will investigate and evaluate the effectiveness of different training modalities (aerobic, resistance and combined) in women living with obesity compared to a non-exercise control. The results of this study will help inform exercise prescription for women living with obesity and will be presented as soon as they are available.

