**Methods and analysis:**

Sixty women (aged 18–50) with obesity (body mass index [BMI] ≥ 30 and/or waist circumference ≥ 88 cm) who are physically inactive, have no unstable health conditions and are safe to exercise will be recruited from September 2021 to December 2022. The main outcome will be feasibility and acceptability of the intervention and procedures. Trial feasibility outcomes will be evaluated to determine if a definitive trial should be undertaken. Trial acceptability will be explored through follow-up qualitative interviews with participants. Secondary outcomes will include CRF (predicted VO_2_ max), anthropometrics (i.e. BMI), strength (5RM bench press, leg dynamometry, grip strength) and other health outcomes (i.e., pain). Participants will be block randomised into one of four trial arms (aerobic exercise, resistance training and combined training groups, non-active control group) and measurements will be completed pre- and post-intervention. The exercise groups will receive an individualised supervised exercise programme for 3× sessions/week for 12 weeks. The change in mean values before and after intervention will be calculated for primary and secondary outcomes. ANOVA and *t*-tests will be applied to evaluate within-group and between-group differences. If sufficient participants are recruited, the data will be analysed using ANCOVA with the age and BMI as covariates.

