### Aims and objectives

Therefore, the primary aim is to evaluate the feasibility and acceptability of prescribed time-matched aerobic, resistance and combined interventions (targeting changes in cardiorespiratory fitness) in women with obesity and to inform whether a future definitive trial could or should be undertaken. We will assess recruitment challenges; retention rates, attendance rates and adherence of participants to prescribed programme, incidence of adverse events and participant’s experience of the intervention and the acceptability of trial procedures and the programmes. We will also collect data from which a power calculation can be based to determine the number of participants needed per group in order to achieve significance in a potential follow-up randomised controlled trial (RCT).

The secondary objectives are to determine the mean difference between groups (three exercise groups and a non-exercise control group) at 12 weeks in:(i)CRF (predicted VO_2_ max)(ii)anthropometric outcomes (Body mass index (BMI), percentage body fat (%BF), lean mass (LM), fat mass (FM), waist-hip ratio (WHR) and waist circumference (WC)(iii)strength (five repetition maximum [5RM] bench press, leg dynamometry, grip strength)(iv)self-reported quality of life, physical activity, sedentary time, sleep, mood and pain

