### Hypotheses tested

Primary null hypothesis: Post intervention, there is no difference in outcomes (CRF, strength, body composition, self-reported) between participants randomised to the exercise interventions and the control.

Secondary null hypothesis: Post intervention, there is no difference in outcomes (CRF, strength, body composition) between participants randomised to the aerobic exercise, resistance training and combined training groups.

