#### Sample size

As this is a pilot study, which has the primary goal of evaluating the feasibility of the interventions and not ensuring there is adequate power to detect between-group differences, a formal sample size calculation is not required [48]. However, the researchers recognise that the sample size will need to be large enough to provide a degree of accuracy around the estimated effect of the interventions on a desired outcome (i.e. between-group difference in CRF which would be the primary outcome in an RCT) which would indicate whether a definitive RCT is worth pursuing. We estimated that we would need to recruit approximately 10% of the number of participants needed for a full-scale RCT. Based on previous research in this area [67], a sample size calculation for a definitive RCT indicates that we would need to recruit 484 participants. Therefore, allowing for 20% attrition, we aim to recruit 60 participants for this pilot study to inform the power analysis for a full-scale RCT.

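### The efficacy outcomes are secondary and not powered for, yet they carry the primary null hypothesis, and the Discussion claims effectiveness and guidance on exercise prescription from them

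*Protocol article*

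**What the plan says.** On what the trial is for, three places agree.

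- Abstract, Methods and analysis: "The main outcome will be feasibility and acceptability of the intervention and procedures". The same paragraph ties the decision on a definitive trial to the feasibility outcomes.
- Aims and objectives: "the primary aim is to evaluate the feasibility and acceptability of prescribed time-matched aerobic, resistance and combined interventions". The efficacy comparisons come next, one level down: "The secondary objectives are to determine the mean difference between groups (three exercise groups and a non-exercise control group) at 12 weeks". They cover cardiorespiratory fitness (CRF), anthropometry, strength and self-report.
- Sample size: the goal is feasibility and "not ensuring there is adequate power to detect between-group differences". CRF is named as the primary outcome of a later randomised trial.

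Four places give the efficacy outcomes a different standing.

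- Hypotheses tested: "Primary null hypothesis: Post intervention, there is no difference in outcomes (CRF, strength, body composition, self-reported) between participants randomised to the exercise interventions"; the comparator is the non-exercise arm. A secondary null compares the three exercise modes on CRF, strength and body composition. Neither hypothesis concerns feasibility.
- Statistical methods: every outcome is tested by ANOVA and t-tests, with significance at p ≤ 0.05.
- Table 2: the title promises both primary and secondary outcomes, but every row is an efficacy or health measure.
- Discussion: the trial will "investigate and evaluate the effectiveness of different training modalities (aerobic, resistance and combined"), and "The results of this study will help inform exercise prescription for women living with obesity".

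The abstract's own Discussion paragraph says only that the pilot will inform future research and a possible full-scale trial.

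**The concern.** The hypothesis called primary concerns no primary outcome. An analyst who follows Hypotheses tested, Statistical methods and the closing Discussion in order has a primary null, a significance threshold for each outcome, and a stated use in exercise prescription. Two poor conclusions are then easy to draw. One nominally significant result among many could be reported as evidence that exercise, or one mode of it, is effective. A non-significant comparison of modes could be reported as showing that the modes do not differ. The Sample size section says that the power needed for such conclusions was not sought.

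**Working it through.** **1. The plan's own figure.** Sample size takes about 10% of 484 and allows for 20% attrition: 0.10 × 484 = 48.4, and 48.4 / 0.80 = 60.5 (48 / 0.80 = 60). The stated 60 reproduces. Allocation 1:1:1:1 gives 15 per arm, or 12 completers per arm after 20% attrition. The 484 cannot be reproduced, because the article does not give its effect size, standard deviation, alpha or power.

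**2. Status, section by section.**

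| Section | Feasibility and acceptability | Efficacy outcomes |
|---|---|---|
| Abstract, Methods and analysis | main outcome | secondary |
| Aims and objectives | primary aim | secondary objectives |
| Sample size | primary goal | between-group power not a goal |
| Hypotheses tested | absent | primary and secondary nulls |
| Table 2 | absent | all rows |
| Discussion | absent | effectiveness, prescription |

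The blur reaches the analysis description. The abstract computes mean change for primary and secondary outcomes, whereas Statistical methods does so for secondary outcomes only.

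**3. False positives, if one significant outcome were read as rejecting the primary null.** The protocol does not state this rule. The calculation shows only what that reading would cost.

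- Outcome count (assumed): at the low end 4, one per domain. At the high end 17: CRF 1; BMI, weight, % body fat, waist circumference, lean/fat-free mass, fat mass and waist-hip ratio 7; strength 3; pain, quality of life, mood, physical activity, sedentary time and sleep 6.
- Independent outcomes: 1 − 0.95^m. For m = 4, 1 − 0.8145 = 19%. For m = 17, 1 − 0.418 = 58%.
- Correlated outcomes: 20,000 simulated null trials per scenario, four arms of 12, one pooled exercise-versus-control test per outcome, two-sided 0.05, equal correlation ρ.

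| Outcomes | ρ = 0 | ρ = 0.2 | ρ = 0.5 | ρ = 0.8 |
|---|---|---|---|---|
| 4 | 18.0% | 17.8% | 16.2% | 11.4% |
| 17 | 58.4% | 53.6% | 39.4% | 21.2% |

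**4. Power for the effect implied by 484.** Assume a two-sided 5% comparison of two groups of n each in the definitive trial, so d = (1.96 + z_power) × √(2/n). In the pilot, power ≈ Φ(d / √(1/n₁ + 1/n₂) − 1.96).

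- 121 per arm (484 / 4), 80% power: d = 2.80 × √(2/121) = 0.36.
  - 12 v 12: Φ(0.36/0.408 − 1.96) = 14%.
  - 36 v 12: Φ(0.36/0.333 − 1.96) = 19%.
- 121 per arm, 90% power: d = 0.42. The highest pilot power is 45 v 15 with no attrition, Φ(0.417/0.298 − 1.96) = 29%.
- 242 per group (484 / 2), 80% power: d ≈ 0.255, giving 9% for 12 v 12 and 12% for 36 v 12.

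The range is about 9% to 29%. If 484 already contained a 20% attrition allowance (about 97 analysed per arm), the top end would rise to 35% (45 v 15, 90% design power, d = 0.47).

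**5. Precision.** The 95% interval for a pair of arms has half-width 1.96 × √(2/12) = 0.80 SD with completers, or 0.72 SD with 15 per arm. That is about twice the implied effect of 0.36, so a non-significant comparison of modes cannot show that they are alike.

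**The case against.** The strongest reply is that the article is openly a pilot and states only one decision, whether to run a definitive trial, which it rests on feasibility. A reader might infer that the document gives two rival answers to what decides the trial. It does not, because no decision is attached to the nulls. The words primary and secondary there may only rank the two hypotheses against each other. That stands, and the point is limited to status and claims.

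A reader might also infer that the efficacy tests are formally confirmatory, or that any single p ≤ 0.05 rejects the primary null. The protocol says neither. Statistical methods introduces these analyses as secondary, and Sample size disclaims power. The error rates above are therefore conditional on a reading and are not properties of a stated rule. The count of 17 is generous, since BMI and weight are almost one variable at fixed height. The power figures rest on an undocumented 484.

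A missing exploratory label, hierarchy or multiplicity adjustment would be no finding by itself, because a fuller protocol or analysis plan may supply it. Sample size also already points to CRF as the effect of interest.

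Finally, the closing Discussion is short, its promise to help inform is soft, and it fixes no analysis. Alone it would be minor.

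What remains is text that contradicts other text: a primary hypothesis on secondary outcomes, and a stated use beyond the one in the abstract. An analysis plan held elsewhere does not correct either statement in the published article.

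**Conclusion.** The point holds as an inconsistency in the status of the efficacy results and the claims made from them. Feasibility keeps its place as the basis for deciding on a definitive trial. The contradiction is in the wording and needs no calculation, since the protocol itself says that between-group power was not sought.

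The numbers show why it matters. Under the unstated one-significant-result reading, the false-positive chance is roughly 11% to 58% against a nominal 5%, for 4 to 17 outcomes and correlations of 0.8 to 0. Power for the effect implied by 484 is roughly 9% to 29%, depending on the contrast, the attrition and the assumed design behind 484. Neither a positive effectiveness claim nor a finding of no difference between modes could be supported. This is more than clerical, because following the sections as written would lead to such conclusions. It does not affect the conduct of the trial.

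**What to change.** 1. Hypotheses tested: drop the primary and secondary null-hypothesis labels, or restate the efficacy comparisons as secondary and exploratory to the feasibility aim. Let CRF lead, since Sample size already names it as the future trial's primary outcome.
2. Statistical methods: make between-group mean differences with 95% confidence intervals the basis for interpretation. Do not use p ≤ 0.05 to declare an effect, or its absence to declare no difference.
3. Discussion: replace the effectiveness and prescription statements with the use given in the abstract's Discussion, informing future research and a possible full-scale trial.
4. Table 2: retitle it as secondary outcome measures.

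The cost is wording only. No participants, visits or data are added, and the inputs for the future power calculation are unaffected. The sponsor gives up significance-based effectiveness claims from the pilot.

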## Data Availability

Data of relevance to the reported findings are included in the main body of the paper with additional data provided as supplementary information. Datasets generated and/or analysed during this study will be made available in an online repository following the conclusion of the study. During the course of the study, all electronic data will be stored on the institution’s encrypted drive and on an institution’s encrypted computer. Along with the hard copies of the data, this computer will be stored in a locked filing cabinet in a locked office in the institution which only the research team have access to.

## Abbreviations

5RM: Five repetition maximum
%BF: Percentage body fat
ANOVA: Analysis of variance
ANCOVA: Analysis of covariance
BMI: Body mass index
CONSORT: Consolidated Standards of Reporting Trials
CRF: Cardiorespiratory fitness
F.I.T.T.: Frequency, intensity, time and type
FFM: Fat-free mass
FM: Fat mass
HR: Heart rate
ICPO: Irish Coalition for People Living with Obesity
ISH: Institute for Sport and Health
LM: Lean mass
PAR-Q+: Physical Activity Readiness Questionnaire for Everyone
RCT: Randomised controlled trial
RPE: Rating of perceived exertion
SPIRIT: Standard Protocol Items: Recommendations for Interventional Trials
SPSS: Statistical Package for the Social Sciences
TFA: Theoretical framework of acceptability
UCD: University College Dublin
VO_2_: Oxygen uptake
VO_2_ max: Maximal oxygen uptake
WHR: Waist-hip ratio
WC: Waist circumference
